## Abstract

Prolonged periods of sitting at work can increase trunk muscle fatigue from the continuous contraction of deep trunk muscles. Insufficient activity of these muscles can decrease muscular support to the spine and increases stress on its passive structures. This can lead to reduced spinal mobility and impaired postural stability. It may also stimulate nociceptor activity leading to pain. However, frequently used recovery modalities such as muscle strengthening and stretching exercises, can be time-consuming, impractical, and difficult to implement in the workplace. Diaphragmatic breathing exercises, which increase the activity of the deep trunk muscles by raising intra-abdominal pressure, seem to be a suitable alternative. However, little is known as to what extent diaphragmatic breathing exercises contribute to the reduction of fatigue induced by prolonged sitting. This paper presents a study protocol that aims to investigate the acute effect of diaphragmatic breathing exercises on recovery of fatigue-induced changes in spinal mobility and postural stability in sedentary middle-aged adults at risk of developing non-specific low back pain. Twenty sedentary adults aged between 25 and 44 years will perform Abt’s fatigue protocol, followed by 1) active recovery using diaphragmatic breathing exercises and 2) passive recovery in the form of lying on the bed, respectively. There will be 1 week of rest in-between. Pre-fatigue, post-fatigue, and after the active and passive recovery, spinal mobility and postural stability will be evaluated using the spinal mouse device and a posturography system, respectively. The electromyography will be used to determine the muscle-fatigue conditions. We hypothesize that active recovery in a form of diaphragmatic breathing exercises would be more effective in restoring spinal mobility and postural stability followed by the fatigue of back and hamstring muscles compared to passive recovery in sedentary adults. Increasing core and respiratory muscle strength via these exercises could be beneficial for overall mobility and stability of the spine. Reducing compressive stress on the passive structures of the spine may be also beneficial for lowering low back pain. Therefore, we believe that diaphragmatic breathing exercises have the possibility to be incorporated into the workplace and contribute to better back health in sedentary middle-aged adults.

**Clinical Trial Registration:** [https://www.irct.ir/trial/67015], identifier [IRCT20221126056606N1].

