## 2 Materials and methods

### 2.1 Study design

This experimental pre-post study is designed to investigate the acute effect of diaphragmatic breathing exercises on recovery of fatigue-induced changes in spinal mobility and postural stability in sedentary middle-aged adults at risk of developing non-specific low back pain. This is a study protocol that will be carried out and reported in accordance with the Standard Protocol Items: Recommendations for Interventional Trials statement (SPIRIT). Figure 1 illustrates the study design. The study has been approved by the ethics committee of the Faculty of Physical Education and Sport, Comenius University in Bratislava (No. 5/2022) and the Ethics Committee of Kerman University of Medical Sciences (IR.KMU.REC.1401.386). It also has been approved by Iranian Registry of Clinical Trials (registration reference: IRCT20221126056606N1).

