#### 2.2.2 Sample size estimation and sampling method

A prior sample size estimation was done using the G*Power software package (version 3.1.9.7) based on the study by Fonta et al. (2021). The input parameters were as follows: statistical test = repeated measures, within - between interaction; effect size F = 0.25; α err prob = 0.05; and power (1 − β err prob) = 0.80. As a result, the total sample size was calculated to be 11 subjects. In consideration of the possibility of dropouts, a slightly larger number of subjects will be recruited to participate in this study. The total sample size would be approximately 20 subjects.

A purposeful sampling strategy will be used and participants based on their age, sedentary behavior, and other relevant factors that are related to the study’s focus and have been explained in inclusion and exclusion criteria section will be selected.

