###### 2.3.2.2.2 Assessment of the spinal mobility

Intersegmental mobility, overall and regional spinal range of motion will be measured in the sagittal plane in the standing position using a Spinal Mouse device (Csuhai et al., 2020). It is a wireless electronic, and non-invasive skin-surface tool for computer-assisted imaging and radiation-free examination (Post and Leferink, 2004). The Spinal Mouse’s reliability and validity have been established in populations that were healthy and symptomatic, including back pain (Topalidou et al., 2014). Before starting the examination, every subject will be registered in Spinal Mouse software with gender, age and randomly allocated study codes. Subjects will be asked to take three different standing positions: relaxed but erect (not corrected), maximal flexion and maximal extension of the spine. After undressing the upper body, spinous processes will be palpated, and C7 and S3 will be marked with a body-marker. Spinal Mouse will run paravertebrally along the spinous processes of marked segments. It makes the system capable of recording the contour of skin above the vertebral bodies in the sagittal plane. Positions include:1. Neutral in standing: Subject will be asked to maintain a relaxed position with the feet shoulder width apart, with straight knees and arms by the side, looking and facing straight horizontally towards the wall.2. Maximal flexion in standing: Subject will be asked to flex the trunk with straight knees as far as possible with slow motion from segment to segment, aiming to touch the ground with fingertips.3. Maximal extension in standing: Subject will be asked to cross arms in front of the chest and extend the trunk as far as possible, keeping the knees straight, without extension of the cervical spine.

No warm-up will be performed before the examination and each test will be done once (Post and Leferink, 2004). The mobility values of the segments, including range of flexion from upright (U-F), range of extension from upright (U-E) and total range from extension to flexion (E-F), will be measured (Csuhai et al., 2020).

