###### 2.3.3.2.3 Assessment of the postural stability

Participants will be asked to stand barefoot on a force plate with their arms relaxed comfortably at their sides. They will be instructed to stand in an upright position with their feet abducted at 10° and their heels separated mediolaterally by a distance of 6 cm. A series of trials will be conducted in a randomized order under varied conditions: tandem stance on a force plate with eyes open, tandem stance on a force plate with eyes closed, tandem stance on a foam mat (Airex Balance Pad) placed on the force plate with eyes open, tandem stance on a foam mat (Airex Balance Pad) placed on the force plate with eyes closed (Zemková et al., 2016). Subjects will perform one set of 30s under each condition. Short rest periods break will be allowed after every two trials (Zemková et al., 2021c).

Postural stability will be assessed using a FiTRO Sway Check (FiTRONiC, Bratislava, Slovakia). The system measures the actual force in the corners of the force plate and calculates an instant position of the CoP (sampling rate: 100Hz, 12-bit AD signal conversion, resolution of the CoP position: less than 0.1mm, measuring range: 0–1,000/s, non-linearity: ±0.02%FS, combined error: 0.03%, sensitivity: 2 mV/V ± 0.25%, overload capacity: 150%/sensor). FiTRO Sway Check has been shown to have good to excellent reliability of CoP variables, according to a recent study by Zemkova et al. (2021) (Zemková et al., 2021c). The Romberg quotient (eyes closed/eyes open (EC/EO) sway ratio) will also be calculated. Under unstable conditions, variables of postural stability will be registered by using the FiTRO Sway Check (FiTRONiC, Bratislava, Slovakia). The device consists of a square platform supported by four springs with an elasticity coefficient of 40N/mm. Shifting the CoP in the horizontal plane leads to changes of body weight distribution to the four corners of the platform. Force acting in each corner is calculated as a product of the coefficient of elasticity of the spring used and vertical distance measured by means of a fine sensor. The analogue signals are AD-converted and sampled by computer at the rate of 100Hz. Calculations of instant CoP position is based on force distribution to the four corners of the platform. Basic parameters of postural stability (i.e., mean CoP velocity and mean CoP displacements in medio-lateral and anterior-posterior directions) will be analyzed (Zemková et al., 2021c).

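### As the abstract states it, every participant does active recovery first and passive recovery a week later, so an order effect on fatigue or recovery cannot be separated from the modality effect

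*Protocol article*

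**What the plan says.** The abstract gives one numbered sequence for all twenty adults: the fatigue protocol, "followed by 1) active recovery using diaphragmatic breathing exercises and 2) passive recovery in the form of lying on the bed, respectively". It adds: "There will be 1 week of rest in-between". The hypothesis is comparative: active recovery "would be more effective in restoring spinal mobility and postural stability followed by the fatigue of back and hamstring muscles compared to passive recovery".

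Section 2.1 labels the design: "This experimental pre-post study is designed to investigate the acute effect of diaphragmatic breathing exercises". The words crossover, counterbalanced and randomised are not used there for the recovery modalities.

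The article mentions randomness twice, and neither mention concerns the order of the modalities. Section 2.3.2.2.2 gives participants "randomly allocated study codes" in the device software. In the postural stability section, "A series of trials will be conducted in a randomized order under varied conditions" refers to the stance conditions. Section 2.2.2 says only how people are selected ("A purposeful sampling strategy will be used") and describes no allocation.

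Section 2.4 models assessment time and an experimental group A versus B. It includes no period or sequence term.

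**The concern.** With a single sequence, the active session is always week 1 and the passive session always week 2. Whatever differs between the weeks is part of the contrast that the trial exists to estimate. The article itself points to several candidates:

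- **Practice.** There are four tandem stance conditions at each assessment. With four assessments (2.3.2) or five (2.4), that is 4 × 4 = 16 to 4 × 5 = 20 sway trials in week 1, all before the passive session.
- **Repeated bout.** By week 2 everyone has completed the full fatigue protocol once, and may respond to it or recover from it differently.
- **Learned breathing.** The technique taught in week 1 may be used, knowingly or not, while lying down in week 2.

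These need not act in the same direction, so the sign of the net bias cannot be predicted. No later analysis can recover the information, because no participant has the other order.

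**Working it through.** **Inputs.** From the article: n = 20, two conditions per person, one sequence, 1 week apart, two-sided α = 0.05. It gives no figure for an order effect, so the effect sizes below are assumptions. The sample-size figure in 2.2.2 plays no part in this check.

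**1. Can modality and period both be estimated?** Take a design matrix with columns for intercept, modality (active = 1) and period (week 2 = 1).
- Fixed order: the rows are (1, 1, 0) and (1, 0, 1). Period = 1 − modality, so the rank is 2 for 3 parameters and the two effects are aliased.
- Both orders present: the rows (1, 0, 0) and (1, 1, 1) are added. The rank is 3 and both effects are estimable.

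**2. What does the paired difference estimate?** Let τ be the modality effect, π the week-2-minus-week-1 effect on the outcome contrast, and λ the carry-over of learned breathing into a later passive session.
- Active first: active − passive = τ − π − λ.
- Passive first: active − passive = τ + π.
- Fixed order, everyone active first: the estimate is τ − π − λ.
- Equal numbers per order: the average is τ − λ/2. The period effect drops out; half of the unequal carry-over stays.

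**3. What does a baseline in each session remove?** Let week 2 shift the value at assessment t by δ(t). The change from baseline to a post-recovery assessment in week 2 then shifts by δ(post) − δ(baseline). If δ is the same at every assessment, this is zero and π vanishes from the modality-by-time contrast. If the response to fatigue or the recovery itself changes, it is not zero. The nonparametric route in 2.4 compares A with B separately at each assessment, so there even a constant shift remains.

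**4. Illustration with no true modality effect.** The paired t statistic has noncentrality d√n, where d is the order effect remaining in the contrast, in SDs of the paired difference. The critical value on 19 df is 2.093.

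| Assumed d | d√20 | Rejection, fixed order |
|---|---|---|
| 0.2 | 0.894 | 13.6% |
| 0.3 | 1.342 | 24.7% |
| 0.5 | 2.236 | 56.5% |
| 0.8 | 3.578 | 92.4% |

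Almost all of these rejections lie on the side to which the order effect points: at d = 0.3 the opposite tail holds 0.06%, at d = 0.5 about 0.002%. In a simulation with 10 per order, a period-adjusted test and no carry-over, rejection stayed between 4.7% and 5.3% for every d from 0 to 0.8.

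**5. Masking.** Suppose a true benefit of 0.66 SD (assumed), which the paired test detects with 79.9% power at n = 20. An order effect of 0.3 SD against it leaves (0.66 − 0.3)√20 = 1.610 and power of about 33%. One of 0.5 SD leaves (0.66 − 0.5)√20 = 0.716 and about 10%.

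**6. Price of a period term.** At 0.66 SD, power is 79.9% on 19 df and 79.7% on 18 df.

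**The case against.** **The fixed order rests on one sentence.** It appears only in the abstract. Section 2 never states an order, the flow diagram is not available here, and the authors use the word respectively loosely elsewhere (in 2.3.2, read literally, it would give each modality a different assessment time). The group A versus group B comparison with a Kruskal-Wallis test, and the within-between interaction used for sizing, would suit separate groups. This stands as a reason to reconcile the text. It does not dispose of the point: the one stated order is fixed, and nothing describes a randomised one.

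**Not every learning effect is confounded.** A reader might infer that the bias equals the whole period effect. The documents do not support that. Section 2.3.2 includes a pre-fatigue assessment and 2.4 uses baseline as a time level. If baseline is repeated in each session, a uniform gain in balance cancels in the modality-by-time contrast. What does not cancel is an order effect on the response to fatigue or on recovery, and recovery is the question.

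**The fatigue stimulus is partly controlled.** Rounds continue until a Borg rating of 17, EMG records fatigue, and loads are chosen beforehand. This narrows the room for a week-2 difference in perceived exertion, but it does not guarantee equal effects on sway, mobility or EMG.

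**The error rates are not a forecast of false claims for breathing.** This is right. If order favours the week-2 condition, nearly all the excess rejections favour passive rest and the main risk is a missed benefit. The SD values are assumptions.

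**Counterbalancing is not a complete cure.** Also right: half of any unequal carry-over of learned breathing remains.

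**Conclusion.** The concern holds in a limited form. Followed as the abstract states it, the plan aliases modality with period, and the aliasing matters for order effects that change the response to fatigue or the course of recovery. Shifts that are constant within a session are harmless only under two conditions that the article does not settle: a baseline in each session, and inference from the modality-by-time contrast.

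The direction and size of the bias are unknown. The rates of about 25% and 56% depend on assumed order effects of 0.3 and 0.5 SD, n = 20 complete pairs and a paired t test. They show sensitivity and do not estimate what will happen. It would go too far to read the article as proof that the order is fixed in practice, or that breathing will be falsely favoured. If the order is in fact randomised, the defect is one of reporting, and the abstract and methods are wrong as printed. In either case the passages need correcting, and a truly fixed order cannot be repaired once the data are in.

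**What to change.** - Randomise participants to active-passive or passive-active order, about 10 per order, from a concealed list. The Discussion describes the study as ongoing, so if enrolment has begun this applies to those not yet started, and a 10:10 split may no longer be reachable.
- Take a pre-fatigue baseline in each session, and say so in 2.3.2.
- In 2.4, specify a within-person model with modality, time and period, and take the modality-by-time contrast as the comparison of interest.
- Report the first-period comparison as a sensitivity analysis for learned breathing. At about 10 versus 10 between persons it has low power and should be described that way.
- State the order in 2.1 and replace the word respectively in the abstract. Reconcile the group A versus B and Kruskal-Wallis wording in 2.4, and the within-between sizing in 2.2.2, with a design in which each person does both conditions. If the order is already randomised, correct the abstract and methods accordingly.

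Cost: a randomisation list, a short amendment and about one degree of freedom. No extra visits, staff or participants are needed for the randomisation itself; repeating the baseline adds assessment time only if it is not already planned in both sessions.

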## 1 Introduction

Modern life have resulted in sedentary behaviors among human societies (Egger et al., 2001; Jans et al., 2007). These behaviors are characterized by low levels of physical activity and an energy expenditure of at least 1.5 metabolic equivalents (Freire et al., 2022). The daily job is a major factor in adults’ sedentary behavior (Kett and Sichting, 2020). Office workers sit for 6.6–10.0 h per day on average (Kett and Sichting, 2020). Continuous contraction of the trunk muscles during prolonged sitting can lead to deep trunk muscle fatigue (Saiklang et al., 2022). Fatigability depends on both the contractile capability of the muscles involved in the task as well as the capacity of the nervous system to provide adequate activation signals to accomplish it (Zemková et al., 2021a). The decreased muscle contractile efficiency and limited capacity of the nervous system can increase articular structural stiffness, and delay muscle response time (Hamaoui et al., 2004). Thus, spinal loading decreases which plays an important role in the mobility of the spine (Yang et al., 2005).

Spinal mobility depends on two anatomical and physiological factors (Hamaoui et al., 2004). The anatomical factor corresponds to articular structural stiffness and determines the range of motion capacity (Hamaoui et al., 2004; Hamaoui et al., 2007). The physiological factor corresponds to muscular excitation (by delayed muscle response time) and determines dynamic mobility capacity (Hamaoui et al., 2004; Hamaoui et al., 2007). These features of the spine may be influenced by prolonged sitting (Hamaoui et al., 2004). While the first one is related to a decrease in the spine’s range of motion, the second one is related to a decrease in spine velocity (Hamaoui et al., 2004). Assessment using the spinal mouse suggests that spinal mobility may be impaired as a result of fatigue induced by prolonged sitting (Lenková and Vasilišinová, 2019). Decreased spinal mobility leads to abnormal lumbar vertebrae movement as a compensatory mechanism (Sung et al., 2014). This exacerbates facet joint instability and increases the risk of experiencing lower back pain (Sung et al., 2014).

Additionally, the combination of decreased muscle contractile efficiency (Tajali et al., 2022), and decreased capacity of the nervous system including insufficient integration of sensory information, and impaired neuromuscular functions under fatigue can alter feedforward and feedback control of postural sway (Akulwar and Mulgaonkar, 2017; Zemková et al., 2021a). For example, fatigued healthy subjects exposed to external perturbations have shown longer activation latencies, an increase in electromyographic amplitude, reduced muscle activity, and increased co-contraction (Zemková et al., 2021a; Zemková et al., 2021b). Also postural control strategies can be altered by acute back muscle fatigue (Johanson et al., 2011). These strategies are similar in healthy individuals when postural demands increased to those used by people with recurrent low back pain. The Zemkova (2021) study discovered that lumbar muscle fatigue can cause alterations in the lumbar spinal curvature, which may play a functional role in explaining the reduced ability to maintain balance when subjected to external perturbations. To measure spinal mobility, the study employed the spinal mouse, while the balance was evaluated using the posturography system (Zemková et al., 2021a). Such an altered postural stability can cause predisposing agents for musculoskeletal disorders, especially low back pain (Hanna et al., 2019; Zhang et al., 2020; Suresh et al., 2021). Due to the fact that low back pain strongly correlates with trunk muscle corset condition (Jabłońska et al., 2021), there is a need to control and recover trunk muscle fatigue.

The muscle fatigue recovery process refers to a return of the functional capacity of body tissues after the onset of fatigue (Yi et al., 2022). Physical exercises play a pivotal role in early intervention and are usually recommended at workplace (Kaeding et al., 2017). Two frequently employed recovery modality types are compensatory exercises and relaxation exercises, both of which can be beneficial for releasing tension and reducing fatigue in the musculoskeletal system (Soares et al., 2019). Compensatory exercises are referred to as short active breaks, involving the discontinuation of job tasks for exercising, and typically include muscle strengthening, flexibility, stretching, and breathing exercises (Soares et al., 2019). Conversely, relaxation exercises are typically performed at the end of the working day and include flexibility, stretching, breathing, and self-massage exercises (Soares et al., 2019). It might also be combined to complementary therapies representing mind-body interventions, such as acupuncture, yoga, Pilates, progressive muscle relaxation and meditation (Soares et al., 2019). Complementary therapies modality seeks to rehabilitate employees with work-related musculoskeletal disorders according to their individual complaints (Soares et al., 2019). Therefore, these exercises do not serve as a primary preventive measure (Soares et al., 2019). Furthermore, it is important to note that the success of a movement-related intervention is reliant on the motivation and adherence of participants (Kaeding et al., 2017). Therefore, short and sharp interventions are recommended as they have been found to achieve high levels of adherence, with an expected compliance rate of approximately 76% (Bell and Burnett, 2009). However, muscle strengthening, stretching, and flexibility exercises can be time-consuming, impractical, and difficult to implement in the workplace. Employers must provide appropriate locations for exercise at adequate intervals to address these issues. To avoid these shortcomings, one can use diaphragmatic breathing exercises during prolonged sitting periods at the workplace. Diaphragmatic breathing involves the contraction of the diaphragm muscle located between the chest and abdomen, which can improve breathing efficiency and oxygen delivery (Dhalla, 2022). Normal respiration, also known as tidal breathing, is driven by a group of muscles known as the “respiratory pump,” with the diaphragm being the major respiratory muscle (Russo et al., 2017). When the diaphragm contracts during normal inspiration, it pushes on the abdomen and causes the lower ribs to expand outwards, generating a trans-diaphragmatic pressure that allows for ventilation of the lungs and gas exchange (Russo et al., 2017). Expiration is generally passive, but the expiratory muscles become active during increased breathing effort. Studies Vostatek et al. (2013); Russo et al. (2017) have shown that optimal respiration requires active control of the diaphragm, with the lower ribs staying low and only expanding laterally during inspiration, while the abdomen expands instead of the chest. Diaphragmatic breathing has been found to facilitate slow respiration, with trained individuals achieving slower respiratory rates and greater diaphragm excursion during slow breathing (Russo et al., 2017). Correct and balanced diaphragm performance has been shown to help maintain abdominal pressure and smooth respiration (Russo et al., 2017; Hamasaki, 2020). Increasing intra-abdominal pressure in turn causes activation of the abdominal wall and pelvic floor muscles (Rasheed et al., 2021). This muscle activation provide posterior and anterolateral and inferior stability, thus increasing overall spinal stability (Rasheed et al., 2021). Kang et al. (2016) reported that intra-abdominal pressure that is produced by the connection of trunk stabilization and respiratory muscles affects waist stability and protects the trunk. Training of respiratory muscles increases muscle firing, proprioception of the diaphragm, low back musculature, deep core musculature, and respiratory muscle strength (Stephens et al., 2017). This can have a positive effect on spinal mobility and postural stability. For example, physiotherapeutic breathing exercises, like yoga and Pilates, have been found equally effective in improving spinal mobility in healthy young women (Csepregi et al., 2022). In addition, Stephens et al. (Stephens et al., 2017) demonstrated improvement of postural stability after 8-week diaphragmatic breathing exercises in healthy persons. The improvement of static and dynamic balance have been also reported in athletes with chronic low back pain (Otadi et al., 2021).

Breathing exercises are also effective in the treatment of musculoskeletal complaints, such as low back pain (Kang et al., 2016; Ahmadnezhad et al., 2020; Otadi et al., 2021). For instance, the activation patterns of trunk muscles change immediately during the lifting task after performing an abdominal drawing-in exercise in subjects with recurrent low back pain (Suehiro et al., 2021). A session of respiratory muscle training can also reduce the activity of some ankle joint muscles while performing overhead squats in athletes with chronic low back pain (Borujeni and Yalfani, 2020).

Although the effect of diaphragmatic, exhalation, and inspiratory breathing exercises on spinal mobility (Kang et al., 2018; Lenková and Vasilišinová, 2019) and postural stability (Tajali et al., 2022; Stephens et al., 2017; Armstrong et al., 2018; D’souza et al., 2021; Farzami and Anbarian, 2020; Roth et al., 2021; Ferraro et al., 2020) has been investigated, there are no studies dealing with their recovery following by prolonged sitting at the workplace. People exposed to repetitive, prolonged sitting at their work are prone of back problems, especially in late middle-age. There is also growing concern over the effects of sedentary lifestyles on the young people’s health. However, prevention programs for them are rare. This paper presents a study protocol that aims to investigate the acute effect of diaphragmatic breathing exercises on recovery of fatigue-induced changes in spinal mobility and postural stability in sedentary middle-aged adults at risk of developing non-specific low back pain.

